**D.3.7 Possible Confounders**

Balance and falls in PD are known to be affected by many factors. Certain medications, such as benzodiazepines, can worsen balance in PD patients.^93^ Depending on the point in their dosing cycle PD severity and dyskinesias (dance-like abnormal involuntary movements) can fluctuate and affect balance. Cognition and a person’s level of physical activity could change over the course of a 4 months study and affect their likelihood of falling.^104^ Therefore, at the baseline and reassessment visit, [name] will administer and record the following assessments:

(1) A medical history: This is to identify the subject’s current medications (subjects will be asked to bring in prescription bottles to every visit) and any new medical issues that could have a significant impact on balance testing (i.e. fracture, stroke). Subjects will be asked to not change any medications during the course of the 16 week study. Specifically patients will be instructed not to start or change doses of amantadine, cholinesterase inhibitors, antidepressants, or benzodiazepines as these may all have significant effects on balance.

(2)PD assessment: The Unified Parkinson's Disease Rating Scale (UPDRS) motor score, a very widely used 30 point scale of severity of PD physical symptoms will be recorded.^105^

(3) Dyskinesia Assessment: This will be measured via a clinical rating scale, the Modified Abnormal Involuntary Movements Score (mAIMS), and an objective measure, the force place dyskinesia rating (see D.5.4).^106, 107^

(4) Cognitive testing: The mini-mental status exam (MMSE) will be used for inclusions and the more in-depth Montreal Cognitive Assessment (MoCA), which has been shown to be sensitive to cognitive deficit in PD, will be used to follow cognitive function at the first and last visit.^109,^ ^110^ In addition the following cognitive tests will be administered: Trail Making A & B, Digit Symbol (WAIS-R), Judgment of Line Orientation, Stroop, Letter-Number Sequencing (WAIS-III), semantic fluency “animals” and “vegetables”, Logical Memory I and II (WMS-R), Boston Naming Test, and Digit Span (WAIS-R).

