Using simulation with PASS 2008 software, we determined (see Table 7), the sample sizes needed to detect the 7.9 point mean difference indicated above with 80% power at significance level 0.049 (allowing for an interim analysis at significance level .001) for correlations between 0.5 and 0.75. The simulation method was based on the Mann-Whitney nonparametric test which is more conservative in this setting than a t-test procedure (that is, using a simple t-test for the simulation would result in smaller required sample sizes). We will adjust for confounders using parametric methods, but used the non-parametric approach for sample size selection to assure that enough subjects are selected for simple comparisons. The Balance Manager Systems Clinical Interpretation Guide for Computerized Dynamic Posturography report test-retest reliability results ranging from 0.66 to 0.98 for the cSOT.^92^ With 0.66 for correlation, we would require 63 subjects per group. Allowing for 10% drop-out we will then plan to recruit 70 subjects per group.

**Table 7. Sample sizes per group needed for 80% power at significance level 0.049 to detect a mean difference in posturography composite change of 7.9.**

| SD at baseline and at follow-up for composite posturography | Correlation between baseline and follow-up composite posturography | SD of difference between follow-up and baseline scores | Sample size per group |
| --- | --- | --- | --- |
| 19.1 | 0.50 | 19.1 | 91 |
| 19.1 | 0.66 | 15.8 | 63 |
| 19.1 | 0.75 | 13.5 | 47 |

D.4.2 Interim Analysis: When half of the targeted subjects have completed the follow-up visit, we will conduct an interim analysis of the primary outcome using a significance level of 0.001. This was felt appropriate to ensure additional safety for patients. The primary outcome analysis and analysis of other outcomes will be presented to the Data Safety Monitoring Committee, which will be made up of a group of researchers not directly involved in this project. Using a small significance level for the interim analysis requires strong evidence of an effect of Vitamin D for consideration of early stopping (We will use a significance level of 0.049 for the final analysis so that the Type I error rate for the primary outcome remains controlled at 0.05.). The details of the methods used at the interim and/or final analyses are described below.

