D.4.3.1 Objective 1 Analysis: The primary analysis will use a Mann-Whitney test to compare the changes from baseline in the cSOT between the placebo and vitamin D groups. We will then use regression methods to adjust for the factors used in randomization, baseline vitamin D level and baseline cSOT, as well as the most important confounders: severity of  motor symptoms of PD (UPDRS motor score) and dyskinesia (clinical dyskinesia scale). With 140 subjects we have more than adequate data to adjust for 4 covariates. Additional covariates that are found to be statistically significant when added to the above model or alter the treatment effect estimate by more than 10% will be included in a second model. In addition to formal tests to compare treatment groups, we will construct 95% confidence intervals for the changes in mean cSOT within each treatment group and for the difference in mean cSOT between treatment groups.

Since Vitamin D serum levels depend on additional factors besides supplementation dose including dietary and sun exposure as well as compliance with study treatment we will perform secondary analyses in which we incorporate serum vitamin D level changes as a covariate in the model allowing us to examine the relationship between cSOT changes and vitamin D level changes.

The use of regression methods assume that residuals follow an approximately normal distribution. If the data do not support this assumption we will consider transformations of the response. If we have more than a few cSOT of zero, we will do a separate analysis of the non-zero scores to determine how this affects our results. We only observed a single cSOT of zero in 20 subjects in our preliminary data, so that we are not anticipating that this will be a significant issue in our study. Also, since we are comparing change from baseline, outliers (other than zero) at a single time point are not likely to result in extreme outliers among the change scores. Hence, other values (besides zero) that are extreme are not expected to have much impact on our results. We will, however, examine the influence of all data points (including outliers) on our conclusions.

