We will then compare changes in strength between the two groups using regression methods. We will examine the relationship between changes in strength and changes in the dynamic balance composite score, the static balance composite score, and turn velocity using linear regression methods. The proportions of the variance in the changes in balance and turn duration measures that are explained by the changes in strength will be obtained. In addition to examining the relationship of changes in strength to changes in balance and turn velocity overall, we will examine the relationship after adjustment for treatment group and the confounding variables described above. As in aim 1, we will conduct a secondary analysis to relate changes in outcomes to changes in serum vitamin D.

D.4.3.3 Objective 3 Analysis: For aim 3, we will use the same approaches as above to compare quality of life measures between treatment groups the NHI and the PDQ-39. As a secondary measure to better understand the effect on fear of falling, we will compare the ABC scales between the 2 groups.

D.4.3.4. Additional Analysis: Even though not the primary aim of the study, we feel it would also be useful to look at changes in motor and cognitive function not measured by the gait and balance tests. Therefore we will analyze the UPDRS motor scores and cognitive measures with the same approach as for the other objectives.

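### The second adjusted model picks its covariates from unblinded outcome data, by significance or by a shift of over 10% in the treatment estimate, so its nominal p-value and 95% interval are mildly optimistic

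*Protocol*

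**What the plan says.** Protocol D.4.3.1 sets three steps for Objective 1.

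1. "The primary analysis will use a Mann-Whitney test to compare the changes from baseline in the cSOT" between the two arms. This is unadjusted.
2. A regression on four named covariates: baseline vitamin D, baseline cSOT, UPDRS motor score and the clinical dyskinesia scale. The plan comments: "With 140 subjects we have more than adequate data to adjust for 4 covariates".
3. A second model with two routes of entry. The first is "Additional covariates that are found to be statistically significant when added to the above model". The alternative is to "alter the treatment effect estimate by more than 10% will be included in a second model".

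The entry rule states no significance threshold, does not limit candidates to baseline values, and makes no allowance for selection in the second model's p-value or interval. The natural pool is D.3.7 (Possible Confounders), where variables are recorded "at the baseline and reassessment visit" and a cognitive battery follows the MMSE and MoCA: "In addition the following cognitive tests will be administered".

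The approach is reused. The end of D.4.3.1 treats root mean square velocity similarly, D.4.3.2 and D.4.3.3 refer back to the same methods, and D.4.3.4 handles UPDRS and cognition "with the same approach as for the other objectives".

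**The concern.** Change-in-estimate screening is a tool for confounding in observational data. Under randomisation a baseline covariate is not a confounder, and any movement it causes in the treatment estimate reflects chance imbalance. Screening this way means looking at the unblinded effect, choosing the model by it, and then reporting that effect as if the model had been fixed. The significance limb also uses the outcome to choose the model, so neither limb leaves the nominal error rate intact.

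The 10% limb has a further fault: its yardstick is the estimate itself. When the estimate is near zero, 10% of it is almost nothing and unrelated covariates qualify. When it is large, few do.

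At stake are the stated 5% error and 95% coverage of one adjusted analysis, and of its counterparts for the other outcomes.

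**Working it through.** **Plan's own figure.** D.4.1 and Table 7 give SD 19.1, correlation 0.66, mean difference 7.9 and significance level 0.049.
- SD of change = 19.1 × √(2 × (1 − 0.66)) = 15.75, shown as 15.8.
- n per group = 2 × (1.969 + 0.842)² × (15.75 / 7.9)² = 62.8, so 63. This agrees with Table 7.
- 63 / 0.90 = 70 recruited per group; 2 × 63 = 126 completers.

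**Candidate pool.** D.3.7 lists 12 cognitive scores after MMSE and MoCA, plus force-plate dyskinesia and medications: 12 + 2 + 1 + 1 = 16. UPDRS and clinical dyskinesia are already in the first model. The number of candidates, K, is assumed to be 5 to 20.

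**Why the 10% limb is badly scaled.** Take one standardised covariate unrelated to outcome.
- SE of the treatment estimate = 15.8 × √(2/63) = 2.82. The median absolute estimate under no effect is 0.674 × 2.82 = 1.90, so 10% of it is 0.19 points.
- Adding the covariate shifts the estimate by about its coefficient (SD 15.8/√126 = 1.41) times its chance imbalance (SD √(2/63) = 0.178). The shift has SD 1.41 × 0.178 = 0.25 points.
- A typical shift therefore exceeds the null threshold of 0.19, but is well below the threshold at the planned effect, 0.10 × 7.9 = 0.79.

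In simulation under no effect, at least one covariate enters through the 10% limb only in about 70% of trials with 5 candidates and 82 to 95% with 10 to 20. At a true effect of 7.9 points and 10 to 20 candidates this falls to 13 to 39%.

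**Error of the second model.** Simulated trials: 126 completers, 1:1, SD of change 15.8, four fixed covariates and K independent baseline candidates that jointly explain 0, 20 or 40% of outcome variance. Each candidate is added singly and kept if p < 0.05 (assumed threshold) or if the estimate moves by more than 10%. The kept set is refitted and treatment is tested two-sided at 0.05, which matches a 95% interval. There is no treatment effect. Each setting has 12,000 runs; simulation SE is √(0.05 × 0.95 / 12,000) = 0.2 points.

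| K | Type I error, rule as written | Coverage, rule as written | Type I error, 10% limb alone | Type I error, all K fixed in advance |
|---|---|---|---|---|
| 5 | 5.2–5.5% | 94.5–94.8% | 3.8–5.4% | 5.0–5.3% |
| 10 | 5.7–5.8% | 94.2–94.3% | 4.0–5.5% | 4.9–5.3% |
| 15 | 5.8–6.5% | 93.5–94.2% | 4.5–6.1% | 4.8–5.4% |
| 20 | 6.2–6.7% | 93.3–93.8% | 4.5–6.5% | 4.7–5.1% |

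The four-covariate model gives 4.6 to 5.3%. A covariate set fixed in advance keeps its error rate; the selection is what raises it.

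**Which limb is responsible.** With 10 to 16 independent candidates, the significance limb alone gives 5.2 to 6.8% and the 10% limb alone 4.6 to 6.3%.

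**Correlated candidates.** With 15 candidates at an assumed pairwise correlation of 0.5, jointly explaining 10% of variance, the second model gives 5.1%. With correlated candidates unrelated to outcome it gives 6.0%, against 5.4% for the four-covariate model in the same run.

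**The case against.** The strongest reply is that nothing confirmatory is touched. That stands. The primary test is an unadjusted Mann-Whitney comparison, the first regression has its covariates fixed, and D.4.2 claims type I error control only for the primary outcome. A reader might infer that the trial's main conclusion is at risk; the documents do not support that.

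Four other stronger readings also fail.

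- *The 10% clause is the culprit.* It is not uniformly optimistic: alone it gives 3.8 to 6.5%, and is conservative when candidates are strongly prognostic. The significance limb does as much or more.
- *The rule steers towards a favourable answer.* It is mechanical, stated in advance and symmetric, and admits covariates that shrink the effect as readily as those that enlarge it.
- *Either adjusted model could be cited, giving 6.6 to 8.7%.* That figure assumes selective citation. The plan orders its analyses and gives no permission to swap them.
- *Post-treatment values will be adjusted for.* The rule does not bar reassessment values, and adjusting for a variable that treatment has changed could bias the estimate. But the plan does not say such values will be used, and the effect has not been quantified.

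It is also fair to say that a candidate list is commonly left to the SAP. Its absence is not the point here: the protocol itself fixes a selection rule, and the rule is a poor one. Mood, quality of life and strength stand under Measures rather than Possible Confounder in Table 5, so 20 candidates is an upper assumption and not a documented pool. Cognitive scores are plausibly correlated, which pulls the error back towards nominal.

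**Conclusion.** The point holds in a limited form. Both entry limbs select the second model from unblinded outcome data, and the 10% limb is scaled so that trivial shifts qualify when the effect is near zero. The second model's nominal p-value and interval are mildly optimistic: at most about 1.7 points of type I error (6.7% against 5%) and 1.7 points of coverage (93.3% against 95%) at 20 independent candidates, less with fewer, and close to nominal with correlated ones. The primary test and the four-covariate model are sound on this point.

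These sizes rest on assumptions that the protocol does not settle: the number of candidates, their prognostic strength and correlation, and a 0.05 entry threshold. The change is worth making because it is nearly free and restores nominal error, not because the damage is large.

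**What to change.** Replace both limbs of the rule in D.4.3.1; removing only the 10% clause would leave the significance limb in place. Either:

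- name the second-model covariates now, restricted to baseline values of variables already collected under D.3.7 and Table 5; or
- select them before unblinding, on pooled treatment-blinded data, by prognostic strength for change in cSOT, with no treatment term in the selection model.

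State that the four-covariate regression is the main adjusted analysis and that the second model is supportive. Apply the same wording to root mean square velocity and turn velocity, Objectives 2 and 3, and D.4.3.4.

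The cost is a few sentences in the protocol or SAP. No extra participants, visits or measurements are needed.

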**Research Plan**

**Objectives:** Based on multiple meta-analyses which show that vitamin D supplementation decreases falls in the elderly we plan to examine the effects of vitamin D supplementation on balance and falls in persons with PD.^8-12^ This project has both training value and great clinical significance for veterans with PD.

**A.1 Objective 1:** To determine if high dose vitamin D supplementation improves balance in persons with PD.

We hypothesize that vitamin D supplementation will improve balance function in persons with PD. Participants will undergo 16 weeks of supplementation with calcium plus high or placebo dose vitamin D. The primary outcome measure will be change in the static and dynamic balance (as measured by computerized posturography) with placebo and high dose vitamin D.^13^

**A.2 Objective 2:** To determine whether vitamin D affects balance primarily through effects on strength or on the central nervous system.

We hypothesize that vitamin D supplementation will at least partially improve balance through effects on the central nervous system. Since an effect of vitamin D upon muscles and strength is established, we will determine the proportion of improvement of balance performance attributable to strength.^14^ We hypothesize that changes in strength will not account for all the improvement seen in balance. By measuring three different areas of balance we will be able to determine if supplementation has effects on static, dynamic, and/or ambulatory balance and the contribution of change in strength to each of these.

**A.3 Objective 3:** To determine if vitamin D supplementation improves balance in a clinically meaningful way.

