In summary, evidence for vitamin D receptors, converting enzymes, and binding proteins in many areas of the CNS implies that vitamin D acts directly on the CNS. Although data from this study will not determine the specific brain regions or mechanisms affected by vitamin D, the data generated will determine if an effect beyond the muscle is evident, and may be used to generate more specific hypotheses regarding localization and mechanism to pursued in future studies.

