We have increased our sample size to accommodate 10% drop-out in our power calculations. However, if subjects dropping out are different from those that do not drop out this introduces bias in our conclusions. If there is more than negligible drop-out we will conduct sensitivity analysis to assess the impact on our results of various assumptions about the reasons for drop-out. Information from participants will be solicited about the reasons for dropping-out to help inform our sensitivity analysis.

The secondary outcome for objective 1 will be analyzed in a similar fashion. For this outcome, root mean square velocity, we will not have the issue of zero scores as we did for the composite posturography measure. The measure of dynamic balance, turn velocity, will also not have the issue of zeros.

D.4.3.2 Objective 2 Analysis: In order to determine if changes in balance are due primarily to changes in strength, we will use regression methods. First we will do analyses similar to above for the static posturography measures (SOT1-SOT3), dynamic posturography measures (SOT4-SOT6), and turn velocity from the iMOBILITY. For the individual dynamic measures, scores of zero will occur more commonly than with the overall composite score and hence we will first compare the proportion of individuals who score zero at baseline, follow-up, and both at baseline and follow-up between the two treatment groups. Descriptive information will be obtained on each of the scores. We will again use the Mann-Whitney test to compare the changes from baseline for each component score between the groups. Composite dynamic and static scores will be obtained by averaging the component scores. The dynamic and static composite scores will be compared using the Mann Whitney test and with regression to adjust for confounders. Again, we expect the composite scores to exhibit few zeros. The influence on our results of zeros (and other data values) will be examined.

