D.5.3 Strength Measures: Subjects will be lead through strength testing using the Biodex machine (see Figure 13). The subjects are seated in the Biodex and one leg is placed in the machine. Subjects are encouraged to flex and extend their leg for 5 repetitions as fast and as hard as they can. This is then repeated on the other side. The Biodex is a computerized dynamometer that we will use in an isometric setting set at 120 range of motion. It gives a constant degree of resistance and is able to record total work and peak torque. This device is more sensitive and has better test, re-test reliability than traditional hand held dynamometers.^88,^  ^112^ The baseline data in and of itself will be very interesting. Persons with PD likely have lower extremities that are weaker than age matched controls, but this rarely has been looked at in a rigorous manner.^95^ [name] has not used this equipment in a research protocol, but our physical therapists have used it clinically in patients with PD with good success.

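### Objective 2 asks what share of the balance improvement is due to strength, but the only proportion planned is variance explained, which does not measure that share

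*Protocol*

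**What the plan says.** Section A.2 of the protocol sets the target: "we will determine the proportion of improvement of balance performance attributable to strength". It adds the hypothesis "We hypothesize that changes in strength will not account for all the improvement seen in balance", next to a hypothesis that vitamin D acts at least partly through the central nervous system (CNS). The closing paragraph of B.4 says that "the data generated will determine if an effect beyond the muscle is evident".

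The analysis is in D.4.3.2, which opens: "In order to determine if changes in balance are due primarily to changes in strength, we will use regression methods". Its steps are:

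- Compare the static, dynamic and turning measures between arms.
- Compare strength: "We will then compare changes in strength between the two groups using regression methods".
- Regress change in each balance measure on change in strength, and obtain "The proportions of the variance in the changes in balance and turn duration measures that are explained by the changes in strength".
- Repeat this within a larger model: "we will examine the relationship after adjustment for treatment group and the confounding variables described above".

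No direct effect, indirect effect or proportion of the treatment effect is named.

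On the strength measure itself, D.3.2 commits the analysis to total work. D.5.3 describes five repetitions of flexing and extending each leg on a dynamometer that "we will use in an isometric setting set at 120 range of motion".

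**The concern.** The objective concerns a share of a treatment effect: of the points gained with vitamin D, how many came through strength? The named statistic is a share of variance between people. It rises and falls with noise in the change scores and with any association between strength and balance that has nothing to do with treatment. Section B.3 itself cites both kinds of quantity from earlier studies: 10% and 26% of balance variance accounted for by strength in one, and up to 22% and 14% of a treatment effect attributed to two aspects of balance in another. The plan computes the first kind to answer a question about the second.

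At stake is the mechanistic conclusion. A low R-squared would appear to support the hypothesis that strength is not the whole story, although a low value is also what full mediation by strength can produce.

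**Working it through.** **Inputs.** From D.4.1 and Table 7: difference in mean change 7.9 points, SD of change 15.8, alpha 0.049 (taken as two-sided), power 80%, 63 per group. These are figures for the composite SOT score (cSOT), used here to set the scale for the static and dynamic composites. The protocol gives no SD, treatment effect or reliability for strength, and no strength-balance correlation, so these are assumed over ranges.

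**The plan's own figure.**
- Effect: 0.9 × 8.8 = 7.9.
- SD of change: 19.1 × √(2 × (1 − 0.66)) = 15.75, stated as 15.8.
- Normal approximation: n = 2 × (1.969 + 0.842)² × (15.8/7.9)² ≈ 63.2, so 64 against 63 stated. A Mann-Whitney simulation with 10% zero changes gives power 0.791 at 63 per group. The figure reproduces.

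**Model.** Let T be treatment (1:1). Strength change is S = aT + error, with within-arm SD 1. Balance change is B = bS + c′T + error. The total effect is ab + c′ = 7.9.

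Var(B) = 15.8² + 7.9²/4 = 249.64 + 15.60 = 265.24.

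Treatment's share of that variance is 15.60/265.24 = 5.9%.

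**All of the effect through strength** (c′ = 0, b = 7.9/a): R² = b²(1 + a²/4)/265.24. For a = 1 this is 62.41 × 1.25/265.24 = 0.29.

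| Strength gain a (within-arm SDs) | 0.75 | 1 | 1.5 | 2 | 5 |
|---|---|---|---|---|---|
| R² when the truth is 100% | 0.48 | 0.29 | 0.16 | 0.12 | 0.07 |

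Smaller gains give larger values: 0.71 at a = 0.6 and 1.0 at a = 0.5. The last requires balance change to be determined by strength change with no noise at all.

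**None of the effect through strength** (a = 0, within-arm correlation r): R² = r² × 249.64/265.24.

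| Correlation r | 0.2 | 0.3 | 0.5 | 0.56 | 0.7 |
|---|---|---|---|---|---|
| R² when the truth is 0% | 0.04 | 0.09 | 0.24 | 0.29–0.30 | 0.46 |

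**Simulation at 63 per arm** (4,000 runs per scenario; median and 2.5th to 97.5th percentiles):

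| Truth | R² | Treatment-adjusted partial R² (median) | Indirect effect | Direct effect |
|---|---|---|---|---|
| 100% (a = 1) | 0.30 (0.17 to 0.43) | 0.25 | 7.8 (4.4 to 11.9) | 0.0 (−5.3 to 5.4) |
| 50% (a = 0.5, r = 0.5) | 0.28 (0.15 to 0.42) | 0.25 | 3.9 (1.2 to 7.3) | 4.0 (−1.0 to 8.9) |
| 0% (a = 0, r = 0.56) | 0.29 (0.17 to 0.43) | 0.31 | 0.0 (−3.2 to 2.9) | 8.0 (3.2 to 12.5) |

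Three different truths give nearly the same R-squared, and adjusting it for treatment does not help. The indirect effect separates the 100% and 0% cases.

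**Ceiling from noise in balance.** D.4.1 quotes test-retest reliability of 0.66 to 0.98 for the cSOT. If the 0.66 correlation is pure test-retest error, all within-arm variance is noise and R-squared under full mediation cannot exceed 5.9%. At 0.98, the error variance of the change is 2 × 19.1² × 0.02 = 14.6, and the ceiling is (265.24 − 14.6)/265.24, about 94%.

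**Noise in strength.** Under classical measurement error the within-arm slope b is multiplied by the reliability of measured strength change. An effect wholly through strength would then read as about 70% at reliability 0.7 and 50% at 0.5 (assumed values), even with the correct estimand.

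**The case against.** The strongest reply is that R-squared is only one step of several. D.4.3.2 also compares strength change between arms and fits a treatment-adjusted regression, and D.4.3.1 already lists baseline cSOT as a covariate. These are most of the parts of a mediation analysis. The two extreme cases above differ in whether vitamin D raises strength by 1 SD or not at all; at 63 per arm the planned comparison would see that difference with z of about √(63/2) = 5.6. This stands: a reader might infer that the plan as a whole cannot tell full from zero mediation, and that is true only of R-squared. What is missing is the statement that the indirect and direct effects are the quantities that answer the objective.

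Two further readings go beyond the text. One is that the protocol declares R-squared to be the share of benefit, or reads unexplained variance as a CNS effect. No sentence says either; the link is that A.2 promises a proportion and D.4.3.2 supplies no other. The other is that the method is biased one way, towards the CNS. In the zero-mediation cases R-squared credits strength with 4% to 46% when the truth is 0%, which errs the opposite way.

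It is also fair that bootstrap details belong in a statistical analysis plan. The choice of measure does not, because the protocol itself fixes it.

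**Conclusion.** The concern holds for the named quantity. Variance explained by strength change cannot answer Objective 2: its range is about 0.07 to 0.48 under full mediation and 0.04 to 0.46 under none, for strength gains of 0.75 to 5 SD and within-arm correlations of 0.2 to 0.7. Those ranges are assumptions, and the 7.9 and 15.8 are borrowed from the cSOT, so the overlap matters and no single value should be quoted as the size of the error. With any noise in the change scores R-squared is below 1 whatever the mechanism, so the stated hypothesis would look supported even if strength carried the whole effect.

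This is a should-fix. B.0 calls the strength question a secondary goal, although E.7 describes understanding the mechanism as a primary objective. Power is assessed only for the cSOT, and the primary comparison is unaffected.

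The isometric wording in D.5.3 is a separate, minor contradiction: a contraction without movement yields no mechanical work, yet total work over repeated flexion and extension is the planned measure. It has no bearing on the R-squared argument. The reliability papers cited for the device have isokinetic in their titles, which suggests a wrong word.

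**What to change.** In D.4.3.2, name the estimands and draw them from models that are largely planned already, in the randomised patients only:

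- Model strength on treatment, baseline strength and baseline balance.
- Model balance on treatment, strength and the same baselines.
- Report the indirect effect, the direct (treatment-adjusted) effect and the proportion mediated, with bootstrap intervals.
- Add sensitivity analyses for error in measured strength and for unmeasured strength-balance confounding. The latter is needed because strength change is not randomised.
- Keep R-squared as a descriptive statistic.
- Word any remainder as an effect not through measured leg strength, rather than as a CNS effect.

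Separately, reconcile the dynamometer setting in D.5.3 with the total-work measure in D.3.2 and D.5.3.

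The cost is revised wording and modest programming on data already to be collected. The price in precision is real: the proportion mediated will have a wide interval. In the simulation the total effect alone ranges from about 2.4 to 13.5 points, so the indirect and direct effects in points should be read first and the ratio second.

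### The one stated covariate set is built around cSOT and reused by reference for other outcomes; naming each outcome's own baseline would be a free gain in precision

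*Protocol*

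**What the plan says.** D.4.3.1 (Objective 1) gives the only explicit covariate list. The primary test is a Mann-Whitney test to "compare the changes from baseline in the cSOT between the placebo and vitamin D groups". Then: "We will then use regression methods to adjust for the factors used in randomization, baseline vitamin D level and baseline cSOT", together with UPDRS motor score and a clinical dyskinesia scale. The list is counted: "With 140 subjects we have more than adequate data to adjust for 4 covariates". Anything further goes into a second model by an entry rule: "Additional covariates that are found to be statistically significant when added to the above model or alter the treatment effect estimate by more than 10" per cent.

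The other outcomes are covered mostly by reference:

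- RMS velocity, end of the Objective 1 text: "The secondary outcome for objective 1 will be analyzed in a similar fashion".
- SOT sub-scores and turn velocity, D.4.3.2: "First we will do analyses similar to above for the static posturography measures (SOT1-SOT3", and so on through the dynamic measures and turn velocity.
- NHP and PDQ-39, D.4.3.3: "For aim 3, we will use the same approaches as above to compare quality of life measures between treatment groups".
- UPDRS and cognition, D.4.3.4: "we will analyze the UPDRS motor scores and cognitive measures with the same approach as for the other objectives".
- Strength, D.4.3.2: changes are compared by regression, with no covariates stated for the group comparison.
- ABC, D.4.3.3: compared between groups, with no method stated.

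No section names an outcome's own baseline as a covariate for any of these, and none says that it is left out.

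**The concern.** For cSOT, the baseline cSOT covariate does two jobs: it is a randomisation factor and it is the outcome's own baseline. The protocol gives only the first reason. When the list is reused for change in PDQ-39, for example, the first job carries over and the second does not. The model then holds the baseline of a different measure and lacks what is usually the strongest predictor of the change.

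The protocol states that power was not assessed for outcomes other than cSOT, so avoidable loss of precision matters more there. Randomisation is stratified only on vitamin D and SOT, so nothing in the design balances baseline quality of life, RMS velocity, turn velocity or cognition, apart from their correlation with those two factors.

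**Working it through.** **Inputs.** From D.4.1 and Table 7: SD 19.1 at both times, correlation r between baseline and follow-up of 0.50, 0.66 or 0.75, difference 7.9, significance level 0.049 (taken as two-sided), 63 evaluable per group. These r values are for cSOT; the protocol gives none for the other outcomes, so their use here is an assumption. Also assumed: correlation q between an outcome's baseline and baseline cSOT of 0 to 0.7, equal SDs at both times, and follow-up related to baseline cSOT only through the outcome's own baseline.

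**The plan's own figures.** SD of change = 19.1 × √(2(1 − r)) = 19.1, 15.75 and 13.51. A normal-theory calculation gives 93, 63 and 47 per group against the stated 91, 63 and 47. A Mann-Whitney simulation with 10% zeros gives power of 0.79, 0.80 and 0.80 at the stated sizes. 63/0.90 = 70. The sample size stands and is not at issue.

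**Residual variance of the change score** (outcome SD = 1):

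- adjusted for baseline cSOT only: 2(1 − r) − q²(1 − r)²
- with own baseline added: 1 − r²

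At r = 0.66 and q = 0: 0.68 against 1 − 0.4356 = 0.5644. √(0.68/0.5644) = 1.098, so the SE is 9.8% larger. At q = 0.5: 0.68 − 0.25 × 0.1156 = 0.6511, and √(0.6511/0.5644) = 1.074.

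Avoidable SE inflation from omitting own baseline:

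| r | q = 0 | q = 0.3 | q = 0.5 | q = 0.7 |
|---|---|---|---|---|
| 0.50 | 15.5% | 14.2% | 11.8% | 8.2% |
| 0.66 | 9.8% | 8.9% | 7.4% | 5.1% |
| 0.75 | 6.9% | 6.3% | 5.2% | 3.6% |

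A least-squares simulation at r = 0.66, q = 0.5 and 63 per arm gave SEs of 0.1453 (unadjusted change), 0.1423 (baseline cSOT only) and 0.1336 (own baseline added). At r = 0.90 and q = 0 the inflation is only 2.6%.

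**Chance imbalance.** The SD of the baseline mean difference is √(2/63) = 0.178 outcome SD. A change score subtracts the imbalance in full, where the regression would subtract only r times it. The remaining error is −(1 − r) × imbalance. At r = 0.66 a typical imbalance gives 0.34 × 0.178 = 0.06 SD, somewhat less if the outcome correlates with cSOT.

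This is not a second harm on top of the precision loss. With q = 0, 2(1 − r) = (1 − r²) + (1 − r)², which at r = 0.66 is 0.68 = 0.5644 + 0.1156. The last term is the imbalance error, and it is the whole of the avoidable variance.

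**Would the second model pick it up?** Own baseline explains a share R² = 1 − (1 − r²)/[2(1 − r) − q²(1 − r)²] of the residual variance: 0.25 at r = 0.50, q = 0, and 0.068 at r = 0.75, q = 0.7. With 126 subjects and 119 residual degrees of freedom, the expected t is about √(119 × R²/(1 − R²)), or 6.3 and 2.9. It would usually meet the significance criterion if it were tried, but the protocol gives no candidate list that ensures it is tried.

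**The case against.** The strongest reply is that the text is ambiguous rather than wrong. In the cSOT model baseline cSOT is the outcome's own baseline, so an analyst could fairly read the cross-references as putting each outcome's own baseline in that place. Covariate detail for secondary outcomes is also commonly left to a statistical analysis plan. The first part stands: a reader might infer that the protocol adjusts other outcomes for baseline cSOT instead of their own baseline, but it never says so. It does not remove the point. The stated reason for including cSOT is its role in randomisation, which holds for every outcome, so a swap would drop a randomisation factor. Neither reading gives a model with both.

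A reader might also infer that every other outcome is affected. It is not. Strength and ABC have no stated set, UPDRS motor score is already in the list (its timing is not stated), and baseline cSOT covers part of the baseline of its own SOT sub-scores.

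The size is fairly challenged too. The correlations are borrowed, D.5.2 claims excellent test-retest reliability for iMOBILITY, and UPDRS motor score or dyskinesia may absorb some of the same variance. All of these reduce the loss. The second model also softens it, though by selection on the data and without a stated precedence between the two adjusted estimates.

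**Conclusion.** The point holds as a modest one: a free improvement, not an error. Taken literally, the main adjusted regressions for change in RMS velocity, turn velocity, NHP, PDQ-39 and cognitive scores omit own baseline. The cost is about 5 to 10% in SE at an assumed r of 0.66, and about 4 to 16% over r = 0.50 to 0.75 and q = 0 to 0.7. It is less if r is higher or the other covariates overlap, and nil if own baseline is in fact used.

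Two stronger conclusions are not supported. Chance imbalance is not left uncorrected: because the responses are changes, it is over-corrected by a factor of (1 − r). Nor is the treatment comparison biased, since over repeated randomisations the error averages to zero and is reflected in the confidence interval. The primary Mann-Whitney test, the cSOT regression and the sample size are untouched, as are the Mann-Whitney comparisons of the other outcomes.

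**What to change.** State in D.4.3.1 to D.4.3.4 that the adjusted regression for each outcome other than cSOT includes that outcome's own baseline value as a pre-specified covariate, in addition to the two randomisation factors, UPDRS motor score and dyskinesia, and that own baseline is not subject to the second-model selection rule. Say that this also applies to strength and ABC, which now have no stated set.

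The cost is one sentence and one degree of freedom per model. Table 5 already schedules the baseline measurements at visits 1 and 1a, so no new data are needed. The change should be made before unblinding.
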